## Abstract

**Background:**

Lumbar disc herniation is a major cause of sciatica and low back pain and imposes a heavy burden on both individual and society. While use of pharmacopuncture, a combined form of acupuncture and herbal medicine, for lumbar disc herniation is widespread in Korea and China, there is a paucity of research.

**Methods/Design:**

This study is the protocol for a three-armed, randomized, patient, physician, and assessor-blinded controlled pilot study. Sixty patients with severe non-acute sciatic pain diagnosed with lumbar disc herniation (NRS ≥ 5, onset between 4 weeks and 6 months) will be recruited and randomized 20 each to the *Shinbaro* pharmacopuncture (pharmacopuncture with acupuncture), acupuncture, and usual care groups, respectively. The 2 acupuncture groups will receive 2 sessions/week of acupuncture alone or with pharmacopuncture for 4 weeks (total 8 sessions), and the usual care group will receive conventional medication 2–3 times/day and physical therapy 2 sessions/week over 4 weeks (total 8 sessions). The initial acupuncture physician will administer acupuncture at 5 acupoints (GB30, BL40, BL25, BL23, GB34) in the 2 acupuncture groups, and mark an additional acupoint. A second acupuncture physician will administer pharmacopuncture to the marked acupoint in the pharmacopuncture group, and acupuncture in the acupuncture group during acupuncture needle retention. The second physician will administer acupuncture and pharmacopuncture in a similar manner in terms of advice and manual stimulation to maintain patient-blinding, treat the patient out of view of the initial physician, remove the additional acupuncture needle immediately, and cover the area with adhesive bandage to maintain physician-blinding. The primary endpoint will be at 5 weeks post-randomization, and the primary outcome will be Visual Analog Scale (VAS) of sciatic pain. Secondary outcomes will be VAS of low back pain, Numeric Rating Scale (NRS) of low back pain and sciatic pain, ODI, SF-36, EQ-5D, and PGIC. Post-treatment evaluations will take place 5, 7, 9, and 12 weeks after randomization.

**Discussion:**

This trial will evaluate the comparative clinical effectiveness of pharmacopuncture for severe non-acute sciatic pain patients diagnosed with lumbar disc herniation with usual care of conventional medicine and that of Korean medicine (acupuncture), monitor its safety, and serve as basis for a large-scale, multicenter trial.

**Trial registration:**

ClinicalTrials.gov NCT02384928, registered 27 February 2015.

## Background

Sciatica occurs due to lumbar disc herniation (LDH) in approximately 90 % of cases, [1] and is characterized by ipsilateral radiating leg pain [2] secondary to an inflammatory response from nerve root irritation [3]. The prevalence of sciatica ranges from 1.6 % in the general population to 43 % in specific working populations [4]. The annual incidence of sciatica in Western countries is estimated at 5 cases per 1,000 adults [5]. Although the natural history of sciatica is known to be favorable in most patients, [6] a sizable percentage (up to 30 %) report pain persisting for 1 year or more [7, 8]. LDH incurs considerable medical expenses, and according to Benefits by Frequency of Disease data from the 2013 Korean National Health Insurance Statistical Yearbook, the number of patients with intervertebral disc disorders (Korean Standard Classification of Diseases (KCD): M50-M51) was 2.5 million, and yearly medical expenses have reached 790 billion Korean won (excluding the Korean medicine sector of the KCD). Low back pain (LBP) was the most frequent disease in both outpatient and inpatient care in National Health Insurance reimbursements for Korean medicine, and the number of patients with intervertebral disc disorders (KCD: M51) was approximately 19,000 and reported medical expenses were 47 billion Korean won in 2013 [9]. As these statistics only include items eligible for reimbursement, total expenses are expected to be much higher taking into account non-reimbursable and indirect expenditures, and lost productivity.

Many randomized controlled trials (RCTs) comparing non-surgical treatment with surgery in LDH patients with sciatica have reported that between-group differences were not significant at long-term follow-up [10, 11]. Though guidelines and experts agree that first-line treatment for sciatica should be conservative, they are divided regarding specific treatment modality [7]. Recently, more multidimensional approaches are being considered in conservative treatment, and are not limited to conventional treatment, but include complementary and alternative medicine (CAM) [12]. According to a 2004 survey, 43 % of peripheral neuropathy patients use CAM to manage symptoms, and many patients cited dissatisfactory pain control with standard medical treatment as the reason for selecting CAM. Most commonly used CAM treatments included acupuncture, chiropractic manipulation, herbal medicine, magnetic therapies, and vitamins [13].

Pharmacopuncture is a treatment that combines two of the most frequently used Korean medicine treatment methods – traditional acupuncture and herbal medicine – by injecting herbal medicine extracts into acupoints. This method prolongs the mechanical and chemical effect of acupuncture and herbal medicine by optimizing acupoint access [14, 15]. Current usage of pharmacopuncture for musculoskeletal diseases in Korea may be roughly estimated from medical service use of patients with spine surgery sequelae at 2 spine-specialty Korean medicine hospitals where 69 % of 702 patients received pharmacopuncture. Taking into consideration the fact that 88 % received acupuncture, a reimbursable item [16], this data suggests that pharmacopuncture is used almost as frequently as acupuncture. Also, the “Korean Medicine Clinical Practice Guideline for Lumbar Herniated Intervertebral Disc in Adults” published by the Korea Institute of Oriental Medicine (a subsidiary organization of the Korea Research Council of Fundamental Science and Technology under the Korean Ministry of Science, ICT and Future Planning) includes pharmacopuncture in major treatment guidelines for Korean medicine doctors (KMDs), recommending bee venom and *Shinbaro* pharmacopuncture amongst others for LDH patients [17].

However, there is a paucity of rigorous RCTs on pharmacopuncture unbefitting its widespread use and inclusion in clinical guidelines for musculoskeletal diseases in Korea. Hence, we will evaluate the effects of a combined treatment of *Shinbaro* pharmacopuncture with acupuncture in non-acute sciatica patients due to LDH through: 1) comparison with usual care in pain severity, functional scales, quality of life, and adverse events to assess its comparative effect and safety; 2) comparison with acupuncture to determine the specific effect of *Shinbaro* pharmacopuncture; 3) comparison of acupuncture and usual care to evaluate the comparative effect of acupuncture; and thus appraise the feasibility of a large-scale clinical trial.

## Methods/Design

### Design and recruitment

This trial is a randomized, patient, physician, and outcome assessor-blinded pilot study with three parallel arms. Participants will be recruited at Jaseng Hospital of Korean medicine, situated in Seoul, Korea, from May to December 2015. Sixty sciatic pain patients with LDH as confirmed by MRI will be recruited from outpatients visiting Jaseng Hospital of Korean medicine, which is a spine-specialty hospital designated as such by the Korean Ministry of Health and Welfare (900,000 outpatient cases per year). Advertisements will also be placed on site at the hospital, online through Internet advertising media, and on the hospital website for further patient recruitment.

### Trial phases

Informed written consent will be obtained from participants at their first visit before data collection. The trial will consist of three stages.

#### Screening

Potentially eligible patients will be screened using inclusion/exclusion criteria. Magnetic resonance imaging (MRI) scans will be conducted to check correlation with physical examinations and confirm LDH diagnosis. Only MRIs taken after the onset of the current episode of sciatic pain will be considered relevant. Additional MRIs will be conducted at the investigation site as needed in participants with no MRIs for the current episode, or in discrepancy between and/or change in current symptoms and prior MRI. After confirmation by physicians of consistency of sciatic pain symptoms and MRI findings, the patient will be randomly allocated to one of three groups – *Shinbaro* pharmacopuncture, acupuncture, or usual care group. The patient will receive 8 sessions of the assigned treatment for 4 weeks. If the patient is on pain medication before enrollment, the medication will be discontinued for at least 1 day before baseline evaluation, and later replaced with a substitute medicine.

#### Intervention (4 weeks)

The *Shinbaro* pharmacopuncture group will receive *Shinbaro* pharmacopuncture and acupuncture, the acupuncture group acupuncture alone, and the usual care group physical therapy and conventional medication, respectively. Each group will receive 8 interventional sessions of *Shinbaro* pharmacopuncture, acupuncture, and physical therapy, respectively, twice a week over 4 weeks, and the usual care group will take an adjunctive 2–3 doses/day of conventional medication. All groups will receive four educational program sessions supervised by physicians once a week. Participants will be required to receive a minimum of six sessions of assigned treatment.

#### Post-treatment (8 weeks)

The primary endpoint will be at 5 weeks post-randomization, which marks the end of the 8 treatment sessions. Additional follow-up evaluations will be conducted after the primary endpoint. At the post-treatment phase, patients will be allowed pain medication intake, as needed, regardless of type or dose, and patterns of use will be investigated at each follow-up evaluation. To encourage attendance of follow-up evaluations and reduce number of drop-outs, all participants will have the choice to be provided with acupuncture and *Shinbaro* pharmacopuncture at the end of the trial phase (12 weeks post-randomization).

### Participants

#### Inclusion criteria

Age 25 years or older, and 55 years or youngerSciatica patients with average sciatic pain on the Numeric Rating Scale (NRS) of 5 or higher during the 3 preceding daysOnset of at least 4 weeks to 6 months previous for current sciatic pain episodePatients whose sciatic symptoms correlate with MRI findings of LDHPatients who have agreed to follow the trial protocol

#### Exclusion criteria

Patients who have received invasive treatments (e.g. nerve blocks, pharmacopuncture, acupuncture) within the past weekNon-spinal or soft tissue pathologies which may cause LBP or sciatic pain (e.g. spinal tumors, rheumatoid arthritis)PregnancyHistory of spinal surgery, or spinal pathologies other than LDH (e.g. spinal dislocation, fracture)Severe progressive neurologic symptoms (e.g. cauda equina syndrome, progressive muscle weakness)Patients for whom acupuncture may be inappropriate or unsafe (e.g. hemorrhagic diseases, blood clotting disorders, intake of anti-coagulation medicine, severe diabetes with risk of infection, severe cardiovascular diseases, or other conditions deemed unsuitable)

### Randomization and allocation concealment

Random numbers will be generated by a statistician unaware of the design and purpose of this study through stratified block randomization in random blocks of 3 (1:1:1) using a computerized random number generator to allocate patients into 3 groups. SAS version 9.1.3 statistical package (SAS Institute, Cary, NC, USA) will be used. The random numbers will be stored in sealed envelopes until an investigator opens each envelope for random allocation. In situations where code break is warranted during the study, such as serious adverse events (SAEs), the principle investigator will contact the other researchers. Randomization will be performed only after the patient has been confirmed to be eligible, received LDH diagnosis through both clinical signs and radiologic evidence, and given written consent for participation. The patients will receive explanations about the two types of acupuncture (*Shinbaro* pharmacopuncture and acupuncture) which will be conducted by KMDs in accordance with recommendations for pharmacopuncture in the “Korean Medicine Clinical Practice Guideline for Lumbar Herniated Intervertebral Disc in Adults” [17]. They will also be informed of the contents of usual care, which will consist of individually tailored physical therapy and conventional medicine from commonly used treatments for LDH in accordance with Korean Health Insurance Review and Assessment Service data. The envelopes will be opened in view of the patient, and to prohibit reuse of envelopes, the patient name and date of opening will be recorded on each envelope and stored in a double-lock cabinet for the entire duration of the trial under the care of a custodian not involved in the study.

### Investigators and blinding

#### Screening researcher

Once the patient has been determined to be eligible and provided written consent, patient data and baseline information will be collected by the screening researcher. Envelopes containing randomization information will be delivered by the custodian to the screening researcher, and after random allocation, the patient will be escorted to the acupuncture or usual care physician.

#### Statistician

The statistician will generate the random allocation table, and keeping the original, will give a copy to the second acupuncture physician.

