### Blinding

The outcome assessor and statistician will be blinded to the three different treatment types, and the patient and initial acupuncture physician will be blinded to the two acupuncture groups. If possible, visiting times will be scheduled so as to avoid patient contact between groups. The secondary acupuncture physician will not record any information in patient charts for secondary acupuncture-blinding in the initial acupuncture physician, patient, outcome assessor, statistician, and study monitoring agent. All researchers will be impartial towards each patient, and will not try to become knowledgeable of patient allocation. The acupuncture, pharmacopuncture, usual care, and patient education program will be conducted according to the predetermined standard operating procedure (SOP). Blinding will be maintained for study duration, and all data will be collected and transferred from paper case report forms to electronic data processing at study completion. Data will be cross-checked for accuracy, and all data will be non-accessible to all researchers except the statistician. A blinding test will be conducted to assess successful blinding in the two acupuncture group participants and the initial acupuncture physician after the second treatment session.

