### Sample size

There are no prior RCTs which have assessed the effect of *Shinbaro* pharmacopuncture in sciatic pain patients due to LDH. Therefore, the purpose of this pilot study is to calculate the sample size and assess the feasibility of a larger trial. A total of 60 participants with 20 patients per group will be recruited in light of the relatively short treatment and follow-up period. Factoring in a 20 % drop-out rate, we anticipate that this will be the minimum recommended number required for a pilot study [34].

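### The statistician is described as blinded, yet generates and keeps the allocation table and alone has access to the data

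*Protocol article*

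**What the plan says.** Four statements in the protocol article bear on the statistician.

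- Randomization and allocation concealment: "Random numbers will be generated by a statistician unaware of the design and purpose of this study".
- Investigators and blinding, Statistician: "The statistician will generate the random allocation table, and keeping the original, will give a copy to the second acupuncture physician".
- Blinding: "The outcome assessor and statistician will be blinded to the three different treatment types". The second physician is also told to chart nothing, so as to protect the blinding of the "initial acupuncture physician, patient, outcome assessor, statistician, and study monitoring agent".
- Blinding, on data handling: "all data will be non-accessible to all researchers except the statistician".

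Concealment at enrolment is described separately: "The random numbers will be stored in sealed envelopes until an investigator opens each envelope for random allocation". The Screening researcher paragraph has a custodian deliver the envelopes to the screening researcher. The Randomization section describes the custodian as uninvolved in the study and places randomization after eligibility, diagnosis and consent.

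**The concern.** An analyst who can read the allocation is not blinded, whatever the plan calls the role. The label matters because the plan relies on it: the Discussion presents randomization, concealment and blinding as the means of removing bias.

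What is at stake is judgement exercised with sight of both arm and outcome. The clearest case is deciding which participants had a major breach of protocol. The opening sentence of Statistical analysis attaches that condition to the intention-to-treat and per-protocol analyses together, so as worded the judgement could reach the primary analysis.

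The same sentence about the table raises a second, weaker question. A copy goes to a treating physician, which places allocation information at the site outside the custodian and envelope route.

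**Working it through.** The plan states no figure on this point, so there is none to reproduce. The check sets the passages side by side and adds one illustration.

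**1. Can both statements about the statistician be true?** Under Statistician, the role creates the table and retains it. Under Blinding, the role does not know the treatments and alone has the data. If the table is readable and the role is one person, both cannot hold. The no-charting rule does not help, because withholding chart entries cannot blind someone who holds the table.

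**2. Is the table coded?** Under Initial acupuncture, a paper with the patient's allocation number is left on the bed. Under Secondary acupuncture physician, that physician then verifies the group and gives the matching procedure. The copied table appears to be the look-up, so it must be readable by its user, and the statistician keeps the table from which it was copied. No separate decoding key is mentioned.

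**3. Are there two statisticians?** The Randomization section uses the indefinite article, which could suggest a separate generator. The Statistician and Blinding paragraphs speak only of the one statistician, and no second role is listed among the investigators. The claimed ignorance of the design also sits uneasily with building a stratified 1:1:1 list and handing it to the second acupuncture physician.

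**4. Which analysis decisions are exposed?** Statistical analysis fixes analysis of covariance for sciatic-pain VAS at 5 weeks and treats the listed secondary scales in the same way. The primary test is therefore not open to choice. Decisions about who had a major breach are exposed. From Sample size: "A total of 60 participants with 20 patients per group will be recruited". One participant is 1/20 = 5% of an arm.

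**5. How much could the physician's copy reveal?** This is an illustration only. Inputs: blocks of 3 at 1:1:1 (Randomization section) and 60 participants. Assumptions: one stratum and complete blocks, since the strata are not named.

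- No information: guess rate 1/3, so 60 × 1/3 = 20 correct.
- Earlier allocations known: the three positions in a block are guessed correctly with probability 1/3, 1/2 and 1. The mean is (1/3 + 1/2 + 1)/3 = 0.611, so 60 × 0.611 = 36.7 correct. The last place in each of the 20 blocks is certain.
- Whole table held: 60 of 60.

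This bears on concealment only if the holder can influence who is enrolled. Under Screening, unnamed physicians confirm that symptoms and MRI agree before randomization. Nothing says that the second physician is not among them, and nothing says that this physician is.

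**The case against.** The strongest reply is that this is an unreconciled description and not proven unblinding. A generator kept apart from the analyst, or a table in arm codes, would preserve the blinding, and the Randomization section's wording is compatible with the former. This stands in part. A reader might infer that analyst blinding does not exist and that the analyst knows all 60 assignments. The article does not establish that. It shows only that the claim of blinding is contradicted by another paragraph and supported by none.

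On concealment the reply is stronger. A reader might infer that a site physician holds every future assignment from the first day and can steer enrolment. The article says only that a copy is given. The whole sequence is the natural reading, but neither timing nor extent is stated. Enrolment runs through the custodian's envelopes and the screening researcher, and the second physician is given no screening or envelope role. That physician must also know each treated patient's group to deliver the procedure and is not listed as blinded, so no stated blinding is breached. What remains is a gap without a safeguard.

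It might also be thought that the analyst may choose between ANOVA and Kruskal-Wallis for the main result. That choice follows the sentences on baseline characteristics and expectancy, and the primary method is fixed separately.

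Finally, this is a pilot, the outcome assessor is separately blinded, and the definition of a major breach may sit in an analysis plan not shown here. These points limit the consequences. They do not reconcile the paragraphs.

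**Conclusion.** The contradiction is real. As written, one role holds the allocation table and sole access to the data while being called blinded. The stated blinding of the statistician cannot be relied on until the Randomization, Statistician and Blinding paragraphs agree. This rests on reading the statistician as one role and the table as readable, which is what the text implies and nowhere denies.

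The extent is the whole table of 60 assignments. Any resulting bias cannot be quantified from the document. It would act through judgements about participants and data, not through the choice of primary test.

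The copy given to the second physician is a secondary risk that needs a safeguard. The article does not show that concealment is broken or that this physician takes part in enrolment.

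**What to change.** **Statistician.** Reconcile the three paragraphs in one of two ways:

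- state that the person who generates the list is not the analyst and has no access to outcome data; or
- have the existing custodian hold the list and give the analyst data labelled A, B and C until the analysis populations and programs are final.

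Under masked labels, treatment-identifying fields must also be withheld until then. Records of conventional medicine and physical therapy would reveal the usual care arm, as would the blinding test, which is given only in the two acupuncture groups.

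**Second physician.** Release each acupuncture-arm assignment only after that patient is randomized, and keep it available for re-checking at all 8 sessions. Alternatively, state that this physician takes no part in screening or in confirming eligibility.

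**Cost.** Protocol and SOP wording, plus minor handling by the custodian already planned. No extra staff or participants are needed. The change should be in place before enrolment, since lost concealment cannot be restored afterwards.
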